### Outcomes

#### Primary outcome

The VAS is a patient-rated outcome which has been validated for pain [18]. This scale is a 10-cm line where zero represents “not painful at all” and ten represents “most painful.” The patient marks an “x” on the line, based on how intense he/she thinks the pain is, and the assessor measures the length from zero to the “x” mark, which is the pain score. Many clinical trials for poststroke shoulder pain use VAS as their main outcomes [10]. In this study, VAS will be evaluated at every visit and the primary endpoint is defined as the mean change of VAS between the baseline and endpoint to show the intergroup difference. The mean differences of the before and after VAS scores within each group will be subordinately evaluated to see the intragroup effect.

#### Secondary outcomes

The pain rating scale (PRS) is also going to be measured for shoulder pain. PRS is another simple and comprehensive patient-rated outcome used to assess pain. It consists of 4 items for intensity (0–10 points), frequency (0–5 points), duration (0–5 points), and aggravating factors (0–5 points). The pain score is the product of the intensity point and the sum of frequency, duration, and aggravating factors points (0–150 points). The reliability and validity of PRS has been evaluated in a previous study [19].

The Fugl-Meyer assessment is a validated tool that assesses physical performance following a stroke [20]. The scale includes the 4 domains of motor function, quality of sensation, passive range of motion, and joint pain, which are assessed using a 3-point scale (0: “cannot perform”; 1: “perform partially”; and 2: “perform fully”). We plan to only measure 8 items for the upper extremity, (Fugl-Meyer assessment of the upper extremity, FMA-UE), i.e., shoulder retraction, elevation, abduction, abduction to 90°, adduction/internal rotation, external rotation, flexion 0–90°, and flexion 90–180°, which follows the precedent [21].

Passive ranges of motion (PROM) for shoulder flexion, abduction, and extension will be measured with goniometer. We will test the maximum angle of passive movement of the shoulder, unless patients suffer from pain.

A manual muscle test (MMT) will also be included to assess muscle strength with a poststroke shoulder injury. Assessors will grade the hemiplegic shoulder on a scale of 0 (no contraction at all) to 5 (complete range of motion against gravity with maximum resistance) [22, 23].

The modified Ashworth scale (MAS) is one of the most frequently adapted scales for poststroke spasticity. The scale was developed and validated as a clinical rating scale to measure tonal abnormality [24]. Assessors should grade from 0 (no increase in muscle tone) to 5 (rigid shoulder on flexion or extension).

The Korean version of the modified Barthel index (K-MBI) is known to be an ordinal scale used to measure performance in activities of daily living [25]. Ten items (personal hygiene, bathing, feeding, toilet use, stair climbing, dressing, bowel control, bladder control, walking, and chair/bed transfers) will be graded on scale of 1 (completely dependent on others to perform) to 5 (completely independent on others to perform), with a maximum total score of 100 points. The reliability and validity of the Korean version of this scale have been studied [25].

The Korean version of the Beck depression inventory (K-BDI) will be also included in the outcome measurement, on the grounds that depression is prevalent in stroke patients and it could have a negative effect on their functional outcomes [26]. This is a patient-rated outcome with 21 items, 0 to 3 points for each item. A higher the total score reflects a more severe level of depression. This scale has also been validated in Korean [27, 28].

Outcome assessors will be licensed TKM doctors who are not involved in the allocation or EA procedures. They are qualified only when they have greater than 1 year of clinical experience. All the secondary outcomes will be evaluated at baseline and at the end of the study. The mean differences between the verum and sham groups will be compared.

#### Blinding index

Patient and assessor blinding will be evaluated separately with a new BI [14]. They are going to be asked which group they think they belong to and select one of the following answers: verum EA group, sham EA group, or unknown. The index score varies from 1 (complete lack of blinding), 0 (consistent with perfect blinding), or − 1 (guessed they were in the opposite group). This will be assessed at the end of study.

#### Safety assessment

At every visit, assessors will ask a post-interventional question pertaining to adverse events. Unpleasant feelings regarding needling, dizziness, allergic reactions, slight pain, bruises, or pinpoint bleeding are expected on an individual basis. The intensity and causality of each adverse event will be evaluated and recorded. If serious adverse events occur, post-management will be properly carried out. The occurrences number of adverse events will be used for statistical analysis.

### Power calculation

The primary endpoint is the mean difference of the VAS scores for poststroke shoulder pain between the baseline and the endpoint. The null hypothesis is that μ_v_ = μ_s_*,* while the alternative hypothesis is *μ*_*v*_ ≠ *μ*_*s*_, where *μ* is the mean difference and *v* and *s* denotes the verum or sham EA group, respectively. A previous study to compare the effectiveness of acupuncture therapy using non-acupoint sham acupuncture on poststroke shoulder pain [29] showed the reductions of VAS scores with means ± standard deviations of 3.52 ± 2.67 in the intervention group and 1.38 ± 2.43 in control group, respectively. Using a two-sided test, under the assumptions of an of 0.05 and (1-β) of 0.8, a sample size of 24 per group has been calculated. Considering a 20% of dropout rate, a total of 60 participants will be enrolled in the trial (30 per group).

### Statistical analysis

A full analysis set is defined as a group of participants who receive 7 or more verum or sham EA sessions with an evaluation of the primary outcome at the endpoint, while a per protocol set is a subset of participants who complete all verum or sham EA sessions as planned in the protocol. We are going to statistically analyze the obtained data, primarily on the full analysis set, as well as, on the per protocol set for the efficacy analysis. Missing values will be imputed by the method of last observation carried forward in the full analysis set.

Demographic information will be tested with a two-sample t-test or Wilcoxon rank sum test for continuous variables and chi-squared test or Fisher’s exact test for categorical variables. When statistically significant differences between groups are found in demographic information, especially age and sex, those will be used as covariates for effectiveness analysis.

Primary and secondary variables will be summarized using the mean ± standard deviation and tested by two-sample t-test or Wilcoxon rank sum test depending on normality of the distribution. If concomitant treatments are significantly different between groups, intergroup effect will be tested by an analysis of covariance with the information of concomitant treatments adjusted. For the intragroup effect, the results of the VAS scores will be tested by paired t-test or Wilcoxon signed rank test. The significance level will be set at 0.05 (two-sided). Statistical analyses will be performed using SAS® 9.4 software (SAS Institute Inc., North Carolina, USA) by an independent statistician ([name]).

The number of adverse events will be presented with a 95% confidence interval on a safety set defined as a subset of participants who receive at least one verum or sham treatment. A chi-squared test or Fisher’s exact test will be carried out to compare the significant differences between groups.

The results of the blinding assessment will be presented as the number of participants per group assignment with the participants’ deductions of their group assignment in a 2 × 3 table. We will consider blinding to be successful in this study if the calculated confidence interval of the new BI includes zero, following the previous study [14].

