#### Dropout criteria

Any participant will be dropped from the study if he or she a) has a belated discovery of any ineligible criteria; b) withdraws consent, wants to cease, or refuses to undergo the EA or sham procedures; c) is lost to follow-up; d) shows serious adverse events and fails to maintain the protocol; e) takes concomitant use of the prohibited drugs or therapies (see the section, Concomitant treatments); f) violates the protocol seriously; or g) is considered inappropriate to keep in the trial by investigators’ clinical experience.

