### Verum electroacupuncture

The detailed procedures of EA are described following the STRICTA 2010 checklist [12, 13].

The regimen of EA therapy is composed based on the TKM’s theory on acupuncture and the clinical experiences of the TKM experts. All the patients in the verum EA group will go through an identical procedure. On the six adjacent acupoints (LI4, LI15, TE14, SI9, SI11, and GB21), placed on only the side with HSP, the acupuncture needles (stainless steel, 0.25 mm × 40 mm, Dong Bang Acupuncture Inc., Republic of Korea) will be inserted at a depth of 10–15 mm and the de qi sensation will be elicited. Park sham guide tubes will be also used in the verum EA group to blind the patients. The locations of each acupoint conforms to the standard defined by the World Health Organization [15]. Subsequently, a low frequency electronical stimulate (STN-111, Stratek, Republic of Korea) will be connected to the tips of needles to provide electrical stimulation at a medium frequency (30 Hz). Needles with electrical stimulation will be retained for 20 min.

Patients should undergo this procedure 3 times a week for 3 weeks (9 sessions in total). During the procedures, the practitioners are not allowed to talk to patients, minimizing other effects. The practitioners will be licensed TKM doctors with at least 1 year of clinical experience. These practitioners cannot assess the outcomes because assessors should remain blinded throughout the whole study.

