### Concomitant treatments

Drugs, such as steroids or nonsteroidal anti-inflammatory drugs, herbal medications, acupuncture, moxibustion, or rehabilitation therapies for shoulder pain in stroke patients are allowed throughout the trial. However, all concomitant treatments for HSP should be maintained with the same dosage and regimen at least 2 weeks before enrollment until the last assessment. If necessary, the participant should take 2 weeks for a run-in period before enrollment. When there are significant changes of concomitant medications in an enrolled participant, he or she will be dropped out.

The typical care for cerebral hemorrhage or infarction, including oral medications (antiplatelet agents, anticoagulants, or neuroprotectants), rehabilitation therapies, traditional herbal medications, acupuncture, moxibustion, and EA therapies except for at the LI4, LI15, TE14, SI9, SI11, and GB21 acupoints will be permitted throughout the study for both groups.

All the treatments that the enrolled patients take will be monitored closely and recorded in case report forms. When any concomitant treatments related to shoulder pain are significantly different between groups, the findings will statistically be adjusted with these data of concomitant treatments.

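### The primary full analysis set requires 7 or more of 9 sessions and an endpoint VAS, so the primary comparison is a completers analysis, and last observation carried forward has nothing to impute for the primary endpoint

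*Protocol article*

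**What the plan says.** In the protocol article, Statistical analysis, the full analysis set consists of "participants who receive 7 or more verum or sham EA sessions with an evaluation of the primary outcome at the endpoint". Efficacy is analysed "primarily on the full analysis set, as well as, on the per protocol set for the efficacy analysis". The second set is narrower: "a per protocol set is a subset of participants who complete all verum or sham EA sessions as planned in the protocol". A safety set, needing at least one treatment, is used for adverse events. No efficacy analysis of all randomised participants is described.

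The same section adds: "Missing values will be imputed by the method of last observation carried forward in the full analysis set". Under Primary outcome, "VAS will be evaluated at every visit", and the primary endpoint is the change from baseline to endpoint.

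Two other sections decide who reaches the full analysis set. Dropout criteria removes, among others, anyone who "withdraws consent, wants to cease, or refuses to undergo the EA or sham procedures", who has serious adverse events and cannot keep to the protocol, who uses prohibited treatment, or whom the investigators judge unsuitable to continue. Concomitant treatments adds: "When there are significant changes of concomitant medications in an enrolled participant, he or she will be dropped out".

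**The concern.** Randomisation makes the arms comparable at allocation. A set defined by sessions received and by presence of an endpoint measurement is chosen later, by events that treatment and pain can influence. A sham participant whose pain worsens and whose medication changes, or a verum participant who finds needling intolerable and refuses to go on, may leave the primary analysis for a reason tied to the outcome. Practitioners know the allocation (Randomization and allocation), and one dropout criterion rests on investigators' judgement.

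Selective loss from verum of those who improve least would exaggerate the benefit. The same loss from sham would hide it. The name of the set invites readers to assume near-complete inclusion, and the planned secondary set applies a stricter version of the same condition, so neither efficacy analysis shows what happens to those who stop early.

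The definition also does not fit the missing-data rule beside it. Requiring an endpoint VAS for entry leaves that rule idle for the primary endpoint, while VAS readings already taken from early leavers go unused.

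**Working it through.** **Inputs.** From Power calculation: mean VAS reduction 3.52 (SD 2.67) with intervention and 1.38 (SD 2.43) with control; two-sided alpha 0.05; power 0.80; 24 per group; 20% dropout; 30 per group. From Verum electroacupuncture: 9 sessions. Assumed, because the documents do not give them: how strongly removal relates to pain change, and how stoppers would change.

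**1. The plan's own figure.** Difference 3.52 − 1.38 = 2.14. Pooled SD = √[(2.67² + 2.43²)/2] = 2.553. The normal approximation gives 23 per group. With the noncentral t distribution, power is 79.4% at 23 and 81.1% at 24, so 24 is reproduced. Inflation: 24/(1 − 0.20) = 30 per group. The sample size is sound. The allowance corresponds to 6 of 30 per arm, or 12 of 60.

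**2. The two rules side by side.** Entry to the set requires an endpoint VAS. The primary variable needs only the baseline and endpoint VAS. No member of the set can therefore lack the endpoint value, and carrying an earlier one forward never applies to the primary endpoint. The participants for whom a missing-data rule matters are those whom the definition removes, and most of them would have some VAS after baseline because it is taken at every visit.

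**3. Upper bound on bias, one arm only.** Suppose the 20% removed from one arm are exactly those who improved least. For a normal variable, the mean of the upper 80% exceeds the full mean by φ(z₀.₂)/0.8 = 0.280/0.8 = 0.350 SD.

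| Arm with selective loss | Bias in that arm's mean | Share of 2.14 | Direction |
|---|---|---|---|
| Sham | 0.350 × 2.43 = 0.85 | 40% | benefit understated |
| Verum | 0.350 × 2.67 = 0.93 | 44% | benefit overstated |

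**4. Weaker selection, still one arm.** If removal depends on a factor correlated ρ with pain change, the bias is ρ × 0.350 × SD. For ρ = 0.3: 0.26 (sham), 0.28 (verum). For ρ = 0.5: 0.43 (sham), 0.47 (verum). The range is 0.26 to 0.47 points.

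**5. Same selection in both arms.** The biases oppose each other: 0.93 − 0.85 = about 0.08 points, or 4% of 2.14.

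**6. Effect on type I error, illustrative.** Assume no true effect, sham fully retained, and a share q of verum excluded whose mean reduction is g points smaller than that of those retained. Bias = q × g. From q = 10%, g = 1 to q = 20%, g = 2.5, the bias runs from 0.10 to 0.50 points and two-sided type I error from about 5.2% to 10.8%.

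**7. Power when all 30 per arm are analysed.** Assume a share q of verum stop early and change like sham. The difference becomes 2.14(1 − q), the verum variance 2.67² + q(1 − q) × 2.14², and the pooled SD follows as in step 1.

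| q | Difference | Pooled SD | Power, 30 per arm |
|---|---|---|---|
| 0% | 2.14 | 2.553 | 89.1% |
| 10% | 1.93 | 2.593 | 80.8% |
| 20% | 1.71 | 2.624 | 70.0% |

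For 80% power the normal approximation needs 29 per arm at q = 10% and 37 at q = 20%.

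**The case against.** Several points on the other side have force.

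- **The loss may be balanced.** Patients and assessors are blinded with a sham device, recruitment is aimed at inpatients, and treatment lasts three weeks. This makes differential loss less likely but does not exclude it. A reader might take 40 to 44% as the expected bias. The documents do not support that: it is a one-arm worst case, and the 20% is an allowance for dropout, not a forecast of participants with fewer than 7 sessions.
- **The data may not be lost.** A reader might infer that the bias is beyond repair because the removed participants' endpoint VAS is never taken. The article does not say so. It says that they are dropped from the study, not whether they are still assessed. The VAS is scheduled at every visit, so an imperfect analysis of partial data is possible. Someone excluded only by the session rule could simply be put back.
- **The two efficacy sets may differ.** One might say that comparing them tests almost nothing. They differ essentially by participants with 7 or 8 sessions, and the article gives no basis for judging how many that would be. What stands is that the comparison cannot inform on those with fewer than 7.
- **No promise is broken.** The article never uses the term intention-to-treat and says that the trial is to explore effectiveness. The idle imputation rule may point to careless wording rather than a deliberate completers analysis. But the article also sets a formal powered hypothesis, and the wording as it stands fixes the set.

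None of this removes the central point. Nor can it be left to an unseen analysis plan, because the article itself states the definition.

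**Conclusion.** The point holds as a fault in how the primary population is fixed and labelled. Followed as written, the plan compares completers, offers only a stricter alternative, and pairs the definition with an imputation rule that cannot act on the primary endpoint.

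The size and direction of the bias cannot be determined from the article. Under stated assumptions it ranges from about 0.08 VAS points (equal selection in both arms), through 0.26 to 0.47 (one arm, correlation 0.3 to 0.5), to a bound of 0.85 to 0.93 (one arm, all the worst responders). All of these assume 20% loss and normally distributed change with the plan's SDs. Because the definition decides who enters the primary comparison, it should be corrected before the data are analysed.

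**What to change.** 1. Define the primary efficacy set as all randomised participants, analysed as allocated, with no session minimum and no endpoint-VAS requirement.
2. State that the endpoint VAS is sought on schedule from everyone who has not withdrawn consent to data collection, whatever number of sessions they received. Separate leaving the procedures from leaving the assessments in Dropout criteria and Concomitant treatments.
3. Replace last observation carried forward with a method that uses the per-visit VAS, for example a mixed model for repeated measures or multiple imputation, with a sensitivity analysis for departures from its missing-data assumption.
4. Keep the 7-session set, renamed, as a supplementary analysis beside the per protocol set.

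The cost is rewording, some extra endpoint assessments over a three-week treatment period, and possibly power. Including partial adherers may dilute the effect: about 81% or 70% power with 30 per arm if 10% or 20% of the verum arm stopped and changed like sham, against 89% with none. The plan should state this openly. It is not a reason to keep the exclusion.

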### Randomization and allocation

Random numbers will be generated by an independent statistician ([name]) using SAS® 9.4 software (SAS Institute Inc., North Carolina, USA). Block randomization with randomly selected block sizes of either 2 or 4 will also be adopted to keep the number of participants in each group as equal as possible at all times with an allocation ratio of 1:1. Of the 60 total participants, 40 will be stratified by site subgroups (20 in Kyunghee University Korean Medicine Hospital and 20 in Wonkwang University Gwangju Medical Center, respectively) and the remaining 20 will be competitively recruited from both sites.

Sealed and opaque envelopes with random numbers will be prepared by the statistician and opened by a study coordinator after eligibility assessment. Participants will be allocated into either the verum or sham EA group in the order of giving the informed consents. The study coordinator will notify the allocated group to practitioners, who will be different from outcome assessors.

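### The primary full analysis set is chosen on events after randomisation (7 or more sessions and an endpoint VAS), so early leavers drop out of the efficacy comparison, possibly unequally by arm

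*Protocol article*

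**What the plan says.** The Statistical analysis section defines the full analysis set as participants who "receive 7 or more verum or sham EA sessions with an evaluation of the primary outcome at the endpoint". The per protocol set requires all sessions. Efficacy is analysed "primarily on the full analysis set, as well as, on the per protocol set for the efficacy analysis". On missing data: "Missing values will be imputed by the method of last observation carried forward in the full analysis set". A third set, with at least one treatment received, is used for adverse events only.

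The Dropout criteria section removes participants from the study for several reasons. Three matter most here:
- criterion (a): "has a belated discovery of any ineligible criteria"
- criterion (b): "withdraws consent, wants to cease, or refuses to undergo the EA or sham procedures"
- criterion (g): "is considered inappropriate to keep in the trial by investigators’ clinical experience"

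On how the arms differ, verum needles "will be inserted at a depth of 10–15 mm and the de qi sensation will be elicited", followed by 30 Hz stimulation. The Sham electroacupuncture section states that sham needles do not penetrate and no current is conducted. On who knows the allocation: "The study coordinator will notify the allocated group to practitioners, who will be different from outcome assessors". The Primary outcome section has the VAS taken at every visit. The Power calculation section allows for 20% dropout.

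**The concern.** A set called full would be expected to hold close to everyone randomised. This one is filtered by attendance and by availability of the outcome, both of which can be affected by the assigned treatment. A patient with six sessions and a recorded endpoint VAS is excluded even though the outcome is known.

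Nothing else in the plan brings these patients back. The per protocol set is narrower, and the one-treatment set serves safety only. LOCF has nothing to fill for the primary endpoint, because a recorded endpoint VAS is a condition of entry.

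The arms differ in what might make a patient stop: penetration, de qi and current on one side, none of these on the other. If more verum than sham patients leave early and they are improving less than average, those who remain in verum look better than the arm as randomised, and the VAS difference is biased towards electroacupuncture. If the selective losses fall on sham, the bias is of the same size in the other direction. The primary estimate would look the same whether or not this had happened.

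**Working it through.** **Inputs.** From Power calculation: VAS reductions of 3.52 (SD 2.67) and 1.38 (SD 2.43), two-sided alpha 0.05, power 0.8, 24 per group, 20% dropout, 30 per group. The number of losses by arm and how far those lost differ from the rest are not in the document. They are assumptions and are varied below.

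**The plan's own figure.** The difference is 3.52 − 1.38 = 2.14 cm. The SD is √((2.67² + 2.43²)/2) = 2.553 cm. The noncentral t gives power 0.794 at 23 per group and 0.811 at 24, so 24 reproduces. Then 24/0.8 = 30 per group. The sample size is not in error, and the 20% allowance amounts to 6 of 30 per arm.

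**Bias from selective loss.** Let kv and ks be the verum and sham participants excluded, and d the amount by which they improve less than their arm mean. Removing k of 30 raises the mean of those left by k·d/(30 − k), so

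bias = kv·d/(30 − kv) − ks·d/(30 − ks).

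Example: kv = 3, ks = 0, d = 2.553 gives 3 × 2.553/27 = 0.284 cm, which is 0.284/2.14 = 13% of the planned difference.

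The type I error is the noncentral t rejection rate with 58 − kv − ks degrees of freedom and noncentrality bias / (2.553·√(1/(30 − kv) + 1/(30 − ks))).

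| Excluded (verum, sham) | d = 0 | d = half an SD (1.276 cm): bias, type I error | d = one SD (2.553 cm): bias, type I error |
|---|---|---|---|
| 1, 0 | no bias | 0.044 cm, 0.0505 | 0.088 cm, 0.0519 |
| 2, 0 | no bias | 0.091 cm, 0.0520 | 0.182 cm, 0.0582 |
| 3, 0 | no bias | 0.142 cm, 0.0549 | 0.284 cm, 0.0696 |
| 3, 1 | no bias | 0.098 cm, 0.0523 | 0.196 cm, 0.0591 |
| 3, 3 | no bias | 0, 0.050 | 0, 0.050 |

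With heavier loss, 6 verum against 3 sham, the bias is 0.18 to 0.36 cm and the type I error 0.057 to 0.077 over the same two values of d.

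**Check by simulation.** In 60,000 null trials of 30 per arm, the lowest scorers on a variable correlated 0.3 with improvement were lost. Verum-only losses of 1, 2 and 3 gave bias 0.050, 0.096 and 0.138 cm and type I error 0.051, 0.052 and 0.055. With no correlation the bias was about zero. Analysing all 60 as randomised in the same trials gave bias within 0.005 cm and type I error 0.049 to 0.051.

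**Price of keeping early stoppers in.** Suppose k verum patients stop early and gain no more than sham. The expected difference becomes 2.14 × (30 − k)/30. Power is for 30 per arm, with the extra verum variance from mixing the two kinds of patient. The last column leaves those k out and assumes no selection.

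| k | Difference, all randomised | Power, all randomised | Power, k excluded |
|---|---|---|---|
| 1 | 2.07 cm | 0.866 | 0.886 |
| 2 | 2.00 cm | 0.838 | 0.880 |
| 3 | 1.93 cm | 0.808 | 0.874 |
| 6 | 1.71 cm | 0.700 | 0.852 |

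**The case against.** The strongest reply is that unequal loss is unlikely here. Recruitment is aimed at inpatients, treatment lasts three weeks, people with hypersensitivity to or fear of acupuncture are excluded before randomisation, and patients are blinded with the same guide tubes, stimulator and noise. All of this lowers the probability of differential loss; none of it rules it out. De qi and current remain on one side only.

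The article does not say who decides removals under criterion (g), so the practitioners' knowledge of allocation is a possible route and not a demonstrated one. Criterion (a) most naturally covers facts that existed at entry and came to light late, which is the least troubling kind of exclusion. How such cases are checked may well be set out in the full protocol. The concern does not depend on either criterion: refusal or loss to follow-up is enough.

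A flow diagram will show how many left each arm, and earlier VAS values from early stoppers can be compared with those of completers. That allows some examination after the fact. It does not correct the primary estimate.

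The bias is small under most of the assumptions tried, and its direction is open. That stands, and it limits how serious the point is.

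Finally, the sample size was set for 24 evaluable per group, and analysing everyone can dilute the effect. That is also true, and the cost is given in the last table.

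**Conclusion.** The concern holds. The primary efficacy set depends on two events after randomisation, no efficacy analysis of all randomised participants is stated, and the LOCF rule cannot act on the primary endpoint. This is a rule the article fixes, not a detail it leaves out.

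The likely effect is modest. With one to three one-sided losses the bias is 2 to 13% of the planned difference, and the type I error reaches at most 0.070. It is nil if losses are unrelated to outcome or are balanced and similarly selected, and it grows only if losses are many and one-sided. These figures rest on assumed numbers of losses and an assumed shortfall of half to one SD. The safety set is not affected. The change should be made because it is cheap and restores the randomised comparison, not because a large error is expected.

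**What to change.** In Statistical analysis:
- Define the primary efficacy set as all randomised participants in their allocated arm. Except only ineligibility shown by records from before randomisation and confirmed without knowledge of allocation.
- Keep the set with 7 or more sessions as a sensitivity analysis.
- Where the endpoint VAS is still missing, use the VAS already taken at each visit, for example in a repeated-measures model, with LOCF as a sensitivity analysis.

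In Dropout criteria, let investigator judgement (g), refusal of procedures under (b) and needling intolerance that emerges later stop the trial procedures only, with VAS assessment continued where consent allows. Patients dropped for serious adverse events, changed concomitant treatment or serious violations would enter the all-randomised set through their earlier VAS values. Continuing their assessments as well would reduce reliance on the model.

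The cost is wording in two sections, one blinded record check per late-found ineligible case, and VAS at the remaining visits for a few patients. Power stays at or above the 80% target with up to three verum stoppers who do no better than sham. It would fall to 0.70 if all six losses allowed for in verum were such patients, so the team should decide whether that case is plausible enough to plan for.

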### Eligibility criteria

#### Inclusion criteria

We will include any man or woman who a) is 19 years of age or older; b) was diagnosed with cerebral hemorrhage or infarction through an examination using computed tomography (CT) magnetic resonance imaging (MRI) at least 2 weeks prior to the enrollment; c) has hemiplegic shoulder pain with a VAS score ≥ 4; d) agrees that any treatments, including analgesics, for HSP will not be changed from the previous 2 weeks prior to the enrollment until the last evaluation, if applicable; and e) has received a full explanation about the research and has given informed consent.

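### Last observation carried forward can impute no primary endpoint, because the full analysis set already requires an endpoint VAS; for the two-point secondary outcomes it enters zero change

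*Protocol article*

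**What the plan says.** All references are to the protocol article; no statistical analysis plan is shown.

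- **Analysis set** (Statistical analysis): the full analysis set consists of "participants who receive 7 or more verum or sham EA sessions with an evaluation of the primary outcome at the endpoint". Efficacy is analysed "primarily on the full analysis set, as well as, on the per protocol set for the efficacy analysis".
- **Missing data** (Statistical analysis): "Missing values will be imputed by the method of last observation carried forward in the full analysis set". No other missing-data rule is given.
- **Primary endpoint** (Primary outcome): "VAS will be evaluated at every visit and the primary endpoint is defined as the mean change of VAS between the baseline and endpoint".
- **Baseline VAS** (Inclusion criteria): an eligible participant "has hemiplegic shoulder pain with a VAS score ≥ 4".
- **Secondary outcomes** (Secondary outcomes): "All the secondary outcomes will be evaluated at baseline and at the end of the study".
- **Dropout** (Power calculation): 24 per group, raised to 30 per group for 20% dropout, 60 in total.

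**The concern.** The imputation rule and the set to which it applies cancel each other for the primary endpoint. A reader who sees LOCF will assume that participants without a final VAS are kept and imputed. In fact they are removed after randomisation. So is anyone with fewer than 7 sessions, even if that person's endpoint VAS was recorded.

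The reasons for leaving listed under Dropout criteria include refusing the procedures, serious adverse events, use of prohibited treatments and loss to follow-up. Any of these could be related to pain or to the allocated treatment. The comparison of those who remain then no longer has the full protection of randomisation.

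The secondary outcomes raise a smaller, separate point. With only two measurements, the last observation before a missing final value is the baseline. LOCF then turns an unknown change into an observed change of zero.

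**Working it through.** **1. The plan's own sample size.** Inputs from Power calculation: VAS reductions of "3.52 ± 2.67 in the intervention group and 1.38 ± 2.43 in control group", two-sided 5% level, 80% power.

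- Difference: 3.52 − 1.38 = 2.14.
- Pooled SD: √((2.67² + 2.43²)/2) = 2.553.
- Two-sample t-test (noncentral t): 23.34 per group, rounded up to 24.
- Dropout: 24 / (1 − 0.20) = 30 per group, 60 in total.

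The stated 24 and 30 reproduce. The calculation plans for 48 evaluable participants and 60 × 0.20 = 12 who are not evaluable, 6 per arm if dropout is equal.

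**2. What LOCF can fill for the primary endpoint.** The endpoint is a change between two values.

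| Component | Can it be missing in the full analysis set? | Can LOCF fill it? |
|---|---|---|
| Baseline VAS | No, a VAS is needed for eligibility | No, a first value has nothing before it |
| Endpoint VAS | No, it is a condition of entry to the set | Nothing to fill |
| VAS at visits in between | Yes | Yes, but it does not enter the endpoint |

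Primary endpoints imputed: 0. Participants left out instead, at the planned rate: up to 12 of 60. The figure of 12 is the planning allowance; actual exclusions could be fewer or more.

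**3. What LOCF does to a secondary outcome.** Let m be the fraction of an arm in the set without the final measure, and μ the mean change in that arm. Assume that those with the measure are representative. Each imputed change is baseline minus baseline, which is 0, so the arm's mean becomes (1 − m)μ.

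- Equal m in both arms: the difference becomes (1 − m)(μ_v − μ_s), an attenuation of m.
- Unequal m: the difference becomes (1 − m_v)μ_v − (1 − m_s)μ_s, which can lie on either side of the true value.

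The document gives no m for secondary outcomes. As an assumed range, 5%, 10% and 20% attenuate a difference by 5%, 10% and 20%. In people: with 24 per arm in the set, one missing member in each arm costs 1/24 = 4.2%.

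The 20% dropout allowance should not be used for m. Most of those participants have no endpoint VAS and are already outside the set. What remains is members who gave an endpoint VAS but not a secondary measure due at the end of the study, so the lower end of the range is the more plausible.

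**The case against.** The strongest reply is that LOCF does no harm to the primary result: as written, it changes that estimate by exactly zero. Participants are lost through the definition of the set, and the plan works as a completer analysis sized for one, with 24 evaluable per group. This stands. It is too strong to say that the planned power is lost, and the fault lies in the set definition and the LOCF sentence taken together.

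A reader might infer a stronger claim, that LOCF biases the VAS difference by a known amount and makes its standard error too small. The document does not support that. Suppose LOCF were applied to all randomised participants, and leavers had achieved half the mean change on average. The planned difference of 2.14 would become:

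- 3.52 × 0.90 − 1.38 × 0.90 = 1.93 with 20% leaving in each arm;
- 3.52 × 0.85 − 1.38 × 0.95 = 1.68 with 30% verum and 10% sham;
- 3.52 × 0.95 − 1.38 × 0.85 = 2.17 with 10% verum and 30% sham.

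These only illustrate a set and a dropout timing that the plan does not state. Someone who leaves midway has fewer than 7 of 9 sessions and is not in the full analysis set at all. The same holds for 2.14 × 0.80 = 1.71, which carries baseline forward for 20% of each arm. It is a VAS figure, and VAS is not a secondary outcome. The illustrations do show why LOCF should not be kept if the set is widened.

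It can also be said that model details belong in an analysis plan that is not shown. That is fair for the details. It does not excuse the conflict, because the article itself fixes both the method and the set to which it applies, and an analysis plan that followed this wording would inherit the conflict.

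**Conclusion.** The point holds in a limited form. In the full analysis set as defined, LOCF imputes no primary endpoint. The primary analysis is a completer analysis that leaves out up to 12 of 60 randomised participants at the planned 20% dropout. This follows from the text and needs no assumption beyond that rate. The direction and size of any resulting bias cannot be derived from the document.

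For secondary outcomes, LOCF enters zero change as though it had been observed. The effect is an attenuation equal to the missing fraction, if that fraction is equal in both arms and the observed members are representative. The practical size is probably small. The sample size needs no correction. The two sentences should be reconciled before the data are analysed.

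**What to change.** 1. **Analysis set.** Remove the endpoint-VAS and 7-session conditions from the primary analysis set, so that it contains all randomised participants. The per protocol set can stay as the supporting analysis.
2. **VAS.** Delete the LOCF sentence. Fit a repeated-measures mixed model to the VAS already recorded at every visit, with arm by visit, baseline VAS and site, and take the endpoint contrast between arms as primary. With 60 participants, use a limited number of visits (for example the last of each week) or a structured covariance, not an unstructured matrix over all visits.
3. **Sensitivity.** The model assumes data missing at random, and someone with no VAS after baseline adds nothing to the contrast. Prespecify one sensitivity analysis under missing-not-at-random.
4. **Secondary outcomes.** Use baseline-adjusted ANCOVA on observed values instead of carrying baseline forward, and report the number missing per arm.

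Cost: no new data and no change in sample size. The stated t-test or Wilcoxon test is replaced as the primary analysis, which is more than a wording change and has to be fixed in advance, and some programming is added.
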